## Abstract

**Background::**

Vascular cognitive impairment (VCI) refers to all cognitive disorders caused by cerebrovascular disorders. For the treatment, many types of pharmacologic and nonpharmacologic treatments are used but their underlying mechanisms and effects are unclear. Regarding nonpharmacologic treatment, electroacupuncture (EA), transcranial direct current stimulation (tDCS), and computerized cognitive rehabilitation treatment (CCRT) are effective. Here, we report the protocol for a randomized controlled trial of the effect and safety of combination therapy of EA or tDCS and CCRT in patients with VCI.

**Methods::**

This study will be a prospective, outcome assessor-blinded, parallel-arm, randomized controlled clinical trial. Participants with cognitive impairment caused by stroke after 3 months of onset (n = 45) will be randomly assigned to a CCRT, combination therapy with EA and computerized cognitive rehabilitation treatment, or combination therapy with tDCS and computerized cognitive rehabilitation treatment group. All groups will receive treatment 3 times per week for 8 weeks, giving a total of 24 treatments. The CCRT group will perform a training task like shopping, calculating, and others and involving computerized cognitive assessment and brain training system (RehaCom) for 30 minutes. The combination therapy with EA and computerized cognitive rehabilitation treatment group will receive EA using 8 acupuncture points – baekhoe, sinjeong, both sides of pungji, 4 sites of sishencong – and will be applied using an EA stimulator and receive CCRT for 30 minutes at the same time. The combination therapy with tDCS and computerized cognitive rehabilitation treatment group will receive tDCS treatment and receive CCRT for 30 minutes at the same time. The primary outcome will be evaluated using the Lowenstein occupational therapy cognitive assessment, while other scales assessing walking ability, activities of daily living, and quality of life are considered secondary outcome measures. Outcomes will be evaluated before intervention, at the end of intervention 8 weeks after the first intervention, and 4 weeks after completion of the intervention program.

**Discussion::**

This study aims to examine the effect and safety of combination therapy with EA or tDCS and CCRT in patients with VCI. This study can be useful in developing new treatment technologies using collaborative research with combined traditional Korean and conventional medicines.

**Trial registration::**

This trial has been registered with cris.nih.go.kr (registration number, KCT 0003644 Registered 01 April 2019, http://cris.nih.go.kr).

## Introduction

1

Vascular cognitive impairment (VCI) refers to cognitive dysfunction attributable to all forms of cerebrovascular disease.^[1]^ It ranges from mild cognitive impairment to dementia caused by cerebrovascular disease.^[2]^ Patients with VCI experience symptoms caused by prefrontal subcortical lesion; detrimental effects on attention, executive functions, planning, and cognitive control; and decreased verbal fluency and memory.^[3]^

A previous study reported that about half of patients with VCI (49%) progress to dementia and the mortality rate of patients with vascular dementia within 5 years as high as 60%.^[4]^ Though cerebrovascular causes of dementia account for approximately 20% to 30% of cases, the frequency of VCI may be higher than expected because of the low rate of treatment in patients with cerebrovascular disease.^[5]^

Alzheimer disease is the most prevalent form of dementia, followed by vascular dementia, which is becoming increasingly important because many cases of Alzheimer disease are associated with vascular factors.^[6]^ In particular, considering that the incidence of cerebrovascular disease and heart disease is increasing in the elderly population and considering the rapid societal aging in Korea, it will be a serious social burden on our society in the future.^[7]^

Since the risk factors for cerebrovascular disease are already known, and treatment and prevention is to some extent possible, treatment and prevention of vascular cognitive disorders resulting from cerebrovascular disease is relatively possible, in contrast to Alzheimer dementia or irreversible cognitive disorders.

Therefore, in patients with a vascular cognitive disorder who have mild cognitive impairment now, but have potential risk factors that can be aggravated, it may help with early diagnosis, prevention, and treatment.

Many clinical trials have reported that various medications are effective in improving vascular cognitive disorders, but there are few medications that are officially licensed.^[8]^ Although medical treatment has the advantage of improving some functional and behavioral aspects of a patient's life, the role of nonpharmacological treatment has primarily been seen as compensation for the limitations of pharmacological therapy because of the potential for controversy over side effects or uncertain efficacy.^[9]^

Electroacupuncture (EA) is a method of treatment that passes a weak current through an acupuncture stimulator after passing through 2 or more acupuncture points to deliver electrical stimuli with needle stimulation in oriental medicine and has been reported to improve cognitive impairment.^[10,11]^

Computerized cognitive rehabilitation is the treatment of a specific area that is affected in a patient using computer programs. It is used in the improvement of cognitive function because it is possible for the patient to self-practice, learn, and repeat the cognitive task. Moreover, the immediate and direct feedback on the result of the treatment is possible and the result of the training task can be saved and progress can be observed.^[12]^

In addition, among the methods that can affect brain activity, transcranial direct current stimulation (tDCS) is used in clinical medicine as a brain stimulation method that increases or decreases the activation of the brain cortex by applying a weak direct-current-generated stimulation between 2 electrodes located on the scalp.^[13]^ tDCS is easier to use than other brain stimulation methods, such as transcranial magnetic stimulation, because it applies stimulation to increase awareness of exercise training protocols or recovery in an environment for recovery and is widely used in special studies as part of the experimental design or evaluation.^[14]^

In this study, we aimed to develop therapeutic technology based on the combination therapy of EA or tDCS with computerized cognitive rehabilitation. Through this clinical trial, we aim to contribute to the diversity of treatment and prevention methods for dementia by developing efficient nonpharmacological treatment techniques through the use of EA, computerized cognitive rehabilitation, and tDCS for VCI.

## Methods

2

### Study design

2.1

This study is a randomized controlled clinical trial with a prospective, outcome assessor-blinded, parallel-arm, 1:1:1 allocation ratio, single-center design. This study is a pilot study comparing the effect between “EA with computerized cognitive rehabilitation” and “tDCS with computerized cognitive rehabilitation” to investigate the effect and safety of combination therapy of EA or tDCS with computerized cognitive rehabilitation. Participants who meet the inclusion and exclusion criteria will be randomly allocated into a computerized cognitive rehabilitation treatment (CCRT) group (n = 15), combination therapy with EA and computerized cognitive rehabilitation treatment (CECCRT) group (n = 15), and combination therapy with tDCS and computerized cognitive rehabilitation treatment (CTCCRT) group (n = 15), for a total of 45 participants. The CCRT group will receive computerized cognitive rehabilitation therapy, the CECCRT group will receive combined EA and computerized cognitive rehabilitation therapy, and the CTCCRT group will receive combined tDCS and computerized cognitive rehabilitation therapy. All groups will receive therapy once a day for 3 days a week (excluding Saturdays and Sundays) for 8 weeks, giving a total of 24 therapies scheduled during the hospitalization period at Chonnam National University Hospital.

The outcomes will be measured before intervention, at the end of intervention, 8 weeks after the first intervention, and 4 weeks after completion of the intervention. The change in cognitive function as assessed using the Lowenstein occupational therapy cognitive assessment (LOTCA) scale will be measured as the primary outcome. The changes in the performance of every day movements will be measured using the Korean version of the modified Barthel index (K-MBI) and changes in health-related quality of life will be measured using the European Quality of Life Five Dimension Scale (EQ-5D-3L). The K-MBI and EQ-5D-3L will be secondary outcomes in this study.

This clinical trial was conducted by the Korea Health Industry Development Institute in 2018, a research project on the development of therapeutic techniques for the prevention of dementia and combination therapy with computerized cognitive rehabilitation (HI18C0546).

The design of this study is summarized in Figure 1. And time table of protocol is summarized in Table 1.

**Figure 1 F1:**
[figure not shown]
The flow diagram for this study.

**Table 1 T1:**
[figure not shown]
Time table of protocol.

### Participant recruitment

2.2

Patients who have finished treatment of the early acute stage of stroke at the Department of Rehabilitation of Chonnam National University Hospital were enrolled. Patients confirmed as stable by a doctor and meeting the inclusion and exclusion criteria will be recruited.

All participants in this study will be given an explanation regarding this protocol by the clinical research coordinator (CRC) and will be able to voluntarily sign a consent form. The CRC will monitor the status of participants in this protocol to improve adherence.

### Inclusion criteria

2.3

Patients will be considered for recruitment if they meet all of the following conditions: patients who are aged from 20 to 90 years, diagnosed with stroke by computerized tomography or magnetic resonance imaging examination, whose score on the Korean version of the Montreal Cognitive Assessment (MoCA-K) is below 22, and who can communicate with others and have no visual disturbance and no difficulty in reading and understanding Korean.

### Exclusion criteria

2.4

Patients who cannot receive treatment due to general ill-health will be excluded. Additional exclusion criteria are as follows: cognitive impairment accompanied by brain tumor, encephalitis, or traumatic brain injury; significant cognitive impairment before stroke; severe depression or psychological disorders that make it difficult to adapt to treatment; change in the medication or other treatment that may affect the symptoms of cognitive impairment within the last month; contraindications to EA (eg, metal in the head or cochlea excluding that in the oral cavity [eg, electrode or stimulator, aneurysm clip or coil, stent, bullet piece, deep brain stimulator, vagus nerve stimulator, or ocular implant], artificial pacemakers, defibrillators, nerve stimulators, drug pumps, intracardiac intravenous line, continuous seizure, cranioplasty, ventriculoperitoneal shunt, sustained symptoms of headache, nausea, and vomiting associated with increased intracranial pressure); contraindications to scalp acupuncture (eg, wound or infections at the acupuncture site on the scalp, hemostatic abnormality due to abnormality of blood coagulation system such as hemophilia, and serious previous adverse reactions after acupuncture treatment); serious medical condition that leaves the patient unable to perform cognitive rehabilitation; musculoskeletal disorders or degenerative motor disorders such as Parkinson disease or Huntington disease that cannot complete a computer program; and pregnant women or women capable of childbearing.

### Ethical considerations

2.5

This study will follow the guidelines of the Declaration of Helsinki for medical research involving humans.^[15]^ Ethical approval was obtained before participant recruitment and the Institutional Review Board of Chonnam National University Hospital has approved this study (CNUH-2019-061). All participants will receive sufficient information and explanation regarding the purpose and potential side effects of this study, and written informed consent will be asked from all participants before participating in this study.

### Randomization

2.6

The treatment allocation into CCRT, CECCRT, or CTCCRT groups in this study will be determined using a randomization process. For this randomization, random allocation software^[16]^ will be used to randomly allocate 15 participants into each group. This randomization process will be conducted by a third-party team of statisticians and the allocations will be concealed and sequentially numbered with opaque and sealed envelopes. The serial number codes will be opened in the presence of the participants and CRC.

### Implementation

2.7

Only the CRC will generate the allocation sequence, enrollment, and assign participants to interventions.

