### Blinding

2.8

This study is a prospective, single-blinded (outcome assessor), parallel-group, randomized controlled clinical trial with a 1:1:1 ratio of participants to be allocated into the CCRT or CECCRT or CTCCRT groups. In this study, each participant will know which program is applied to them. Therefore, we have adopted a single blinding (outcome assessor blinding) approach. To maintain the objectivity of this study, we have separated the outcome assessor, CRC, and therapist who treats the participant. In this study, individuals with conflicts of interest or preconceived positions are excluded to prevent related bias.

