### Data management

2.16

The participants in this study will be required to voluntarily sign the consent form before beginning this protocol; the data will then be collected. All data from this study will be recorded and documented or recorded in Excel files by the CRC and all collected data will only be used for research purposes. Personal data including name and resident registration number will not be recorded or used. For data security, all data will be secured in a double locked cabinet until the end of this study and will only be accessible by investigators. Investigators who monitor the data include the principal investigator, resident in charge of EA, occupational therapist in charge of CCRT, doctor in charge of tDCS, and the CRC.

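### Sections 2.6 and 2.7 contradict each other on who generates the allocation sequence, so allocation concealment is not assured

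*Protocol article*

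**What the plan says.** Section 2.6 (Randomization) describes allocation software that puts 15 participants in each group, and states who runs the process: "This randomization process will be conducted by a third-party team of statisticians". It then gives the concealment mechanism: "the allocations will be concealed and sequentially numbered with opaque and sealed envelopes". On opening, it says: "The serial number codes will be opened in the presence of the participants and CRC".

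Section 2.7 (Implementation) consists of one sentence: "Only the CRC will generate the allocation sequence, enrollment, and assign participants to interventions".

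Two other sections bear on the point. Section 2.2 (Participant recruitment) has the CRC explain the protocol to candidates before they sign consent. Section 2.8 (Blinding) lists the roles kept apart: "we have separated the outcome assessor, CRC, and therapist who treats the participant".

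**The concern.** Allocation concealment requires that whoever decides on eligibility and approaches patients cannot know the next assignment. Section 2.6 is built to achieve that. Section 2.7, taken at its word, removes it, because the same person makes the list, recruits and assigns.

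The stakes are higher than usual here. The trial is single-centre, participants and practitioners know the treatment, and each arm has 15 patients. Concealment is therefore one of few protections against bias. Some exclusions in Section 2.4 rest on judgement, such as general ill-health or a psychological state that makes treatment hard to follow, so a recruiter who knew the next assignment would have room to steer. Selection at entry cannot be reliably repaired in the analysis.

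**Working it through.** The plan gives no figure to reproduce. The check is a comparison of the text, followed by an illustration of scale.

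**1. Can both sections hold?**

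| Step | Section 2.6 | Section 2.7 |
|---|---|---|
| Generate the sequence | Third-party statisticians (they conduct the process) | CRC only |
| Conceal it | Numbered, opaque, sealed envelopes | Not mentioned |
| Enrol | Not stated | CRC only |
| Assign | Codes opened with participant and CRC present | CRC only |

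The rows on enrolment and assignment can be reconciled. The row on generation cannot: the word *only* in 2.7 leaves the statisticians no part in making the sequence.

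**2. What follows under each reading?**

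- If 2.6 is followed, the CRC sees an assignment only when an envelope is opened. Concealment is adequate as described.
- If 2.7 is followed, the CRC wrote the list, explains the trial to candidates (Section 2.2) and enrols them. A sealed envelope cannot hide a sequence from its author. Up to 45 of 45 assignments (3 × 15) are known in advance. That count restates the premise of 2.7 and is not separate evidence.

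**3. Does another section resolve it?** Section 2.8 separates assessor, CRC and therapist. It does not separate the person who makes the sequence from the person who enrols, so it leaves the conflict open.

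**4. Scale, by illustration.** The inputs of 3 steered patients and 1 SD are assumptions; only the 15 per arm is from the plan. The SD is that of the change in the primary outcome, the LOTCA score.

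- One arm steered: 3 of its 15 patients have an expected change 1 SD better than those who would otherwise have entered. Shift = (3/15) × 1 SD = 0.2 SD.
- Two arms steered in opposite directions, 3 patients in each: shift = 2 × 0.2 = 0.4 SD.
- Standard error of a difference between two arms of 15: √(1/15 + 1/15) = √(2/15) = 0.37 SD.
- The smaller shift in standard errors: 0.2/0.37 ≈ 0.55.
- Two-sided 5% test with no true effect, normal approximation: P(Z > 1.96 − 0.55) + P(Z < −1.96 − 0.55) ≈ 0.079 + 0.006 ≈ 0.085, a false-positive rate of about 8.5% instead of 5%.

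**The case against.** The strongest reply is that 2.6 shows what was intended. It names the type of software, an independent team and a complete envelope procedure, whereas 2.7 is a single ungrammatical sentence that could be a slip for saying that the CRC enrols and assigns. On that reading concealment never failed. This stands as a limit on the conclusion: a reader might infer that concealment fails, but that holds only if 2.7 describes practice, and the article does not say so. That the CRC would hold the list is likewise an inference from generating it, though a direct one. The reply does not remove the contradiction, because nothing tells site staff which section governs.

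A second reply is that the illustrated bias is modest beside the noise. This also stands: 0.2 SD is about half a standard error, so the example shows an inflated error rate and not a manufactured effect.

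A reader might also go further and infer from Section 2.16 that assessor blinding is weakened, since the CRC records all data and treating staff are among those who monitor them. The documents do not show this. Recording scores is not rating patients, Section 2.8 keeps the assessor apart from the CRC and the therapist, and Section 2.17 gives the analysis to a statistician not involved in the study. Nothing in the text shows allocation reaching the assessor. That is a separate and weaker matter, and it forms no part of this point.

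**Conclusion.** The contradiction is established: two adjacent sections of current text name different parties as the source of the allocation sequence. It is an internal inconsistency, and not a detail that an article would leave to a fuller document, since the article states both versions. The consequence is conditional. Concealment is not assured, and it would be lost for the recruiting CRC if 2.7 were followed as written.

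The documents support no estimate of bias. The 0.2 SD figure, or 0.4 SD with opposite steering in two arms, rests wholly on the assumed number of steered patients and the assumed 1 SD difference; it shows scale only. The point still needs correction, because the defect concerns a main safeguard of a small open trial.

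**What to change.** Rewrite Section 2.7 to agree with Section 2.6, for example:

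> The third-party statisticians generate and hold the sequence and prepare the envelopes. The CRC enrols participants and opens the next numbered envelope only after consent, eligibility and baseline assessment are recorded.

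The participant's presence at opening, as in 2.6, can stay.

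If 2.6 already describes practice, the cost is wording only. If 2.7 describes practice, it is an operational change: sequence generation passes from the CRC to the statisticians already named in the plan, with no new personnel. If any participants have already been enrolled, the trial report should state who generated and held the sequence for them.

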### Blinding

2.8

This study is a prospective, single-blinded (outcome assessor), parallel-group, randomized controlled clinical trial with a 1:1:1 ratio of participants to be allocated into the CCRT or CECCRT or CTCCRT groups. In this study, each participant will know which program is applied to them. Therefore, we have adopted a single blinding (outcome assessor blinding) approach. To maintain the objectivity of this study, we have separated the outcome assessor, CRC, and therapist who treats the participant. In this study, individuals with conflicts of interest or preconceived positions are excluded to prevent related bias.

### Intervention

2.9

All participants will receive CCRT in a sitting position, which focuses on cognition improvement. CCRT consists of screening and a treatment program, and these programs are available for pre and posttreatment evaluation. It is possible to automatically apply the treatment program according to the evaluation result and train a range of abilities from basic cognition (attention, memory) to higher cognition (metacognition). In addition, the real-time measurement automatically adjusts the difficulty according to the user's ability.

Participants will be selected for the program after screening tests have been conducted after enrollment. The screening test is composed of 5 types, and the training program is composed of 5 areas, giving in total 23 programs. Participants then perform the treatment tasks (shopping, scheduling, logical thinking, calculation) of the “executive functions” program of the computerized cognitive treatment system (RehaCom Training Test) for 30 minutes.

CECCRT group will receive EA treatment during the period of CCRT. EA will be performed in the sitting position at baekhoe (GV20), sinjeong (GV24), both sides of pungji (GB20), and 4 sites of sishencong (EX-HN1), in total 8 acupuncture sites according to a previous study.^[17]^ Acupuncture needles will be sterile, stainless steel, and disposable (size, 0.25 × 30 mm; Dong Bang Acupuncture, Inc, Boryeong, Republic of Korea; product no. A84010.02). During EA, guide tubes and an EA stimulator (CELLMAC PLUS [STN-330]; Stratek, Co, Ltd, Anyang, Republic of Korea; product no. A16010.04) will be used. The needles will be subgaleally inserted at an angle of 15° to 30° along the scalp at GV20, GV24, and EX-HN1. The needles will be directed in the direction of the tip of the nose at a depth of 17 to 40 mm at GB20. GV20 and GV24 will be inserted anteriorly direction along the scalp at a depth of 15 to 45 mm depth at GV20 and 15 to 24 mm at GV24. Anterior EX-HN1 will be punctured anteriorly, while the right, left, and posterior EX-HN1 will be punctured in the direction of GV20 at a depth of 9 mm.^[18]^ During CECCRT, manual stimulation will not be used. GV24 and GV20, left and right EX-HN1, anterior and posterior EX-HN1, and left and right GB20 will be subjected to EA under the following parameters: continuous waves; frequency, 3 to 15 Hz; and intensity, 2 to 4 mA for 30 minutes.^[17]^

The CTCCRT group will receive tDCS treatment during the CCRT period. The tDCS treatment will be conducted in the sitting position as follows. Two electrodes and a HDC stimulator (HDC kit, YoungWoo med, Korea) will be used to deliver 1 mA of tDCS to the skull. The anode is attached to F3, the anterior epidermal area of the left lateral cerebral hemisphere (dorsolateral prefrontal cortex) and the cathode is attached to the upper side of the right eye. The intensity and conduction time, which are stimulus parameters, are applied at 1 mA for 30 minutes when applying tDCS.^[19,20]^

The CCRT will be conducted by an occupational therapist from the Department of Physical and Rehabilitation Medicine at Chonnam National University Hospital. EA will be conducted by a doctor from the Dongshin Traditional Korean Medicine University Hospital, who has more than 2 years of clinical experience in Korean medicine. tDCS will be conducted by a doctor from the Department of Physical and Rehabilitation Medicine at Chonnam National University Hospital.

All participants will receive treatment once a day for 3 days a week (excluding Saturdays and Sundays) over 8 weeks, giving a total of 24 scheduled therapy sessions at Chonnam National University Hospital.

During the period, routine existing medications for hypertension, diabetes, hyperlipidemia, and other medications do not affect cognitive function will be continued. Other treatments that can affect cognitive function including other rehabilitation programs will not be permitted during this period. All medical devices, including the acupuncture needles, EA stimulator, tDCS, and RehaCom software, will be inspected by the investigators who will record the results of check-ups in the management register.

